### Procedure for unblinding if needed {17b}

As the design is open label, unblinding will not occur.

## Data collection and management

### Plans for assessment and collection of outcomes {18a}

Variables will be assessed (1) online via self-report measures and (2) via the questionnaire proposed by the APA teacher at the beginning and at the end of the APA sessions. Primary outcomes will be assessed at baseline, 3 months, 6 months (end of the study), and at 3 and 6 months’ follow-up for all arms. Secondary outcomes will be assessed at baseline, 6 months (end of the study), and 6 months’ follow-up. Sociodemographic variables will be assessed at baseline only.

### Plans to promote participant retention and complete follow-up {18b}

Participants will be contacted for follow-ups via email. Participants will not be offered additional incentive to complete the trial. However, the questionnaires will be available online, and they are as short as possible which reduces the burden of its completion.

### Data management {19}

The principal investigator will send to each participant a study participant number in order to identify them throughout the trial. The biostatisticians and the principal investigators involved in the study will monitor data entry and check for any missing, abnormal, or extreme data.

### Confidentiality {27}

All data will be stored on local servers of the Upper Alsace University, and the access to the file is restricted to the principal investigator via a key locker according to GDPR policy and the PIA. All data will be kept strictly confidential, and the data from the participant will be pseudonymized (study participant number).

### Plans for collection, laboratory evaluation, and storage of biological specimens for genetic or molecular analysis in this trial/future use {33}

See the “Additional consent provisions for collection and use of participant data and biological specimens {26b}” section; there will be no biological specimens collected.

## Statistical methods

### Statistical methods for primary and secondary outcomes {20a}

General linear models and multilevel analyses comparing the difference in mean scores between groups with repeated measures will be performed. Two-sided *p* < .05 will be considered statistically significant. Moderation and mediation analysis will also be performed. Statistical analysis plan will be adjusted according to the occurrence of unpredictable events. Sensitivity analyses will be performed to investigate the possible influence of missing data on the robustness of the results. Results will be reported according to the CONSORT—Consolidated Standards of Reporting Trials. The statistical analysis plan can be found on osf (https://osf.io/34unj).

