## Outcomes {12}

### Primary outcome measure

The aim of the study is will be to investigate potential change in QoL between baseline, middle (3 months) and end of the study (6 months), and 3- and 6-month follow-up. Greater improvements are expected in the APA + education arm compared to the waitlist control group.

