### Sample size {14}

Two hundred participants will be recruited. This sample size was chosen for several reasons: lack of article on the topic and resource limitations [55]. Except for one, all previous studies recruited or planned to recruit a sample size below 200. Furthermore, the specialists working on the project receive between 5 and 30 endometriosis patients per week. By taking the smallest number of patients and considering the possibility that these patients may refuse to participate or fall into the exclusion criteria, we can assume that only 2 women per week will be included in the study (*N* = 2 × 7 hospitals × 20 weeks of recruitment = 280). Of these participants, 20% may drop out of the study (*N* = 224). We performed sensitivity analyses for repeated measures ANOVA analysis. Effect sizes found were small to medium (*N* = 200 to be more conservative, *α* = 0.05, *β* = 0.90).

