## Assignment of interventions: allocation

### Sequence generation {16a}

Participants will be randomized to one of the four arms using complete randomization which consist of uniformly distributing them. This procedure is performed using an R script. We opted for this procedure to avoid selection bias as this is the only procedure that does not permit to guess the assignment (Supplementary Material). Moreover, it minimizes various bias and various methods allows to correct the bias provoked by unbalanced in arms [56].

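### The primary QoL model as described takes baseline as one of its time points and states no adjustment for baseline EHP-30; adjusting would gain precision at almost no cost, unless the unseen SAP already does so

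*Protocol article*

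**What the plan says.** Three places in the protocol article bear on the primary model.

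- *Primary outcome measure*: the aim is to "investigate potential change in QoL between baseline, middle (3 months) and end of the study (6 months), and 3- and 6-month follow-up". Baseline is therefore one of five measurement times. The contrast of interest follows: "Greater improvements are expected in the APA + education arm compared to the waitlist control group".
- *Sample size {14}*: "We performed sensitivity analyses for repeated measures ANOVA analysis", at "N* = 200 to be more conservative, *α* = 0.05, *β* = 0.90" (the 0.90 is labelled β but is read here as power).
- *Statistical methods for primary and secondary outcomes {20a}* describes the main analysis in a single sentence: "General linear models and multilevel analyses comparing the difference in mean scores between groups with repeated measures will be performed". The test level is also given: "Two-sided *p* < .05 will be considered statistically significant". No covariates are named, and the details are referred elsewhere: "The statistical analysis plan can be found on osf".

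Two further sections concern imbalance. *Sequence generation {16a}* chooses complete randomisation, names no stratification or blocking, and notes that "various methods allows to correct the bias provoked by unbalanced in arms" without naming a method. *Methods for additional analyses {20b}* gives one concrete rule: subgroup analyses if sociodemographic characteristics turn out to differ between arms. That rule does not cover baseline QoL.

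*Concealment mechanism {16b}* requires the baseline questionnaire to be completed before allocation, so a pre-randomisation EHP-30 score should exist for every participant.

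**The concern.** Read together, the objective, the design model and the analysis sentence suggest a repeated-measures model in which baseline is simply the first level of time. An unconstrained model of that kind can yield two different arm effects, and the text does not say which is meant.

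- The group-by-time contrast at a visit is the difference between arms in change from baseline. It subtracts the whole baseline difference, although only a fraction ρ of it is expected to persist to follow-up.
- The group main effect averages all five visits. One of these precedes treatment and cannot show an effect.

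Both are less efficient than a comparison of follow-up scores adjusted for baseline. The key contrast is between two of four arms, so about 50 participants each, and allocation is unstratified. Precision is therefore not plentiful, and chance differences in baseline QoL are to be expected.

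**Working it through.** **Inputs from the protocol.** N = 200, allocation 1:1:1:1, so 200/4 = 50 expected per arm; two-sided α = 0.05; target power 0.90; five time points; 20% dropout. Applying the dropout to 50 gives 40 per arm. This is a cautious case, because the protocol takes the 20% from 280 (giving 224) and then adopts 200.

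**Assumptions.** The protocol prints no baseline-to-follow-up correlation ρ and no numeric effect size. I take ρ from 0.3 to 0.8 and, for illustration, an effect of 0.5 SD. Outcome SD is set to 1.

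**The plan's own figures.** Recruitment: 2 × 7 × 20 = 280, and 280 × 0.8 = 224; both reproduce. For repeated-measures ANOVA with 4 groups, 5 times, N = 200 and 90% power, under compound symmetry and sphericity, the detectable f at ρ = 0.3 / 0.5 / 0.7 is:

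- between groups (λ = f²·N·m/[1+(m−1)ρ], m = 5): 0.18 / 0.21 / 0.23
- group by time (λ = f²·N·m/(1−ρ)): 0.124 / 0.105 / 0.081

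On the usual scale (0.10 small, 0.25 medium) this broadly fits the plan's verbal description. It can be matched only in words, since neither f nor ρ is printed.

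**Precision at a single visit.** The variance of the arm difference is (2/n) times:

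- change from baseline: 2(1−ρ)
- baseline-adjusted: 1−ρ²
- ratio, adjusted to change: (1+ρ)/2

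With n = 50, √(2/50) = 0.20. The detectable difference at 90% power is (1.960 + 1.282) × 0.20 × √factor. Power at 0.5 SD is Φ(0.5/[0.20√factor] − 1.96).

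| Assumed ρ | Factor, change | Factor, adjusted | Ratio | Detectable, change / adjusted (SD) | Power at 0.5 SD, change / adjusted |
|---|---|---|---|---|---|
| 0.3 | 1.40 | 0.91 | 0.65 | 0.767 / 0.618 | 56% / 75% |
| 0.5 | 1.00 | 0.75 | 0.75 | 0.648 / 0.561 | 71% / 82% |
| 0.6 | 0.80 | 0.64 | 0.80 | 0.580 / 0.519 | 80% / 88% |
| 0.7 | 0.60 | 0.51 | 0.85 | 0.502 / 0.463 | 90% / 94% |
| 0.8 | 0.40 | 0.36 | 0.90 | 0.410 / 0.389 | 98% / 99% |

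At ρ = 0.5 the noncentral t gives 69.7% and 81.5% with 50 per arm, and 59.8% and 72.2% with 40 per arm. A simulation of 20,000 trials at ρ = 0.5 gave a variance ratio of 0.758, against 0.75 in theory.

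**Average of the four post-baseline visits** (compound symmetry, ρ = 0.5). The variance of a four-visit mean is (1+3ρ)/4 = 0.625. Change: 0.625 + 1 − 2ρ = 0.625. Adjusted: 0.625 − ρ² = 0.375. The ratio is 0.60, so the gain is larger than at a single visit.

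**Response to chance imbalance.** With 50 per arm, the baseline difference between two arms has standard error 0.20 SD, and 95% of such differences lie within about ±0.39 SD. The expected slope of each estimate on that difference, at ρ = 0.5, with values from a 4,000-trial simulation in brackets:

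- group-by-time (change): −(1−ρ) = −0.50 (−0.49), an over-correction
- group main effect over five visits: (1+4ρ)/5 = +0.60 (+0.60), a partial carry-through; a constant treatment effect is also diluted to 4/5
- baseline-adjusted: 0 (0.01)

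A baseline gap of 0.20 SD thus moves the change estimate by 0.5 × 0.20 = 0.10 SD in the opposite direction, and the five-visit main effect by 0.6 × 0.20 = 0.12 SD in the same direction.

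**The case against.** The strongest reply is that the protocol never says baseline is excluded as a covariate. The analysis section names a family of models and lists no covariates. Its wording also fits a multilevel model of post-baseline scores with baseline as covariate, or one with a common baseline mean. In the latter, baseline is a time point and no precision is lost, so listing it among the visits proves nothing by itself. The other two sources are an objective and a power calculation, and covariates are ordinary SAP content. This stands: a reader might infer that the plan rejects baseline adjustment, but that goes beyond the text.

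A reader might also infer that chance baseline imbalance goes uncorrected, or that the estimate is biased. Neither follows. The talk of change and improvement points towards group-by-time, which removes baseline in full and, if anything, over-corrects. It is unbiased over randomisations. Only a main-effect or follow-up-only comparison would leave imbalance in, and the protocol selects neither.

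Finally, the gain depends on a correlation the protocol does not give. If the change analysis already had 90% power with 50 per arm, adjustment would raise it to 98.0% at ρ = 0.3 and 96.3% at 0.5, but only to 94.0% at 0.7 and 92.7% at 0.8.

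What the reply does not remove is that the three sections most naturally describe baseline as a level of time, that none states an adjustment, and that the one concrete imbalance rule concerns sociodemographic characteristics and answers with subgroup analyses, which do not adjust the arm contrast for baseline QoL.

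**Conclusion.** The point holds as a conditional one about efficiency and clarity. The protocol describes a repeated-measures comparison with baseline among the time points and states no adjustment for baseline EHP-30. If that model is unconstrained, its group-by-time contrast is valid but gives away precision: the adjusted variance would be 0.65 to 0.90 of the change-score variance at one visit for ρ between 0.3 and 0.8. At ρ = 0.5, 50 per arm and a 0.5 SD effect, this is about 82% power instead of 70 to 71%. Near ρ = 0.8 the gain is small. A five-visit main effect would be the poorer choice, because it dilutes the effect and retains part of any baseline difference. The correlation and effect size are assumptions, and the SAP may already settle the matter. The change is worth making because it is nearly free, not because the described analysis would be invalid.

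**What to change.** In *Statistical methods for primary and secondary outcomes {20a}*, define the primary model as post-baseline EHP-30 scores with fixed effects for arm, visit, arm-by-visit, baseline EHP-30 and baseline-by-visit. Equivalently, keep baseline in the outcome vector and constrain its mean to be equal across arms. Take the combined-arm versus waitlist contrast from that model.

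Make the adjustment unconditional, so that it does not depend on whether an imbalance is observed. Apply the same form to the pain and fatigue scales and the other continuous outcomes, each with its own baseline.

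If the SAP on OSF already specifies this, bring the protocol sentence into line with it. The cost is a sentence and one or a few degrees of freedom. No new data are needed, because the baseline questionnaire is already a condition of allocation.

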### Interim analyses {21b}

No interim analyses are planned.

### Methods for additional analyses (e.g., subgroup analyses) {20b}

If the sample size of 200 participants cannot be reached, the data from APA and APA + education arms will be gathered together, and the same protocol will be planned for control group and education arm. If sociodemographic characteristics differ between arms, subgroup analyses will be performed according to the differences found. However, the sample size and the randomization procedure should prevent these issues.

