### Trial design {8}

The study will be a multicentric randomized-controlled superiority trial which will include four arms (i.e., “APA,” “education,” “APA + education,” and “waitlist control group”) and will test the effect of a 6-month program on QoL in patients with endometriosis. The efficacy of the program in intervention groups will be compared to a control group (i.e., waitlist group control) which will benefit from APA and education sessions at the end of the 6 months program. Randomization will be balanced with a 1:1:1:1 ratio for patients’ allocation to the three intervention groups and the waitlist control group. Identifying potential moderators and mediators of treatment outcome will also be a component of this trial.

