## Interventions

### Explanation for the choice of comparators {6b}

The comparator will be the waitlist control group. As much as all participants, those in the waitlist control group will continue with their usual treatment and activities during their participation to the study (e.g., hormonal treatment, antalgic treatment, PA, physiotherapy). The allocation in a group being done randomly, and because each endometriosis case is unique in terms of symptoms and treatment, using a waitlist control seemed relevant to compare the effects of the interventions on participants with similar characteristics. For ethical reasons, the waitlist control group will benefit from the intervention after the and on the main intervention (i.e., 6 months after they start the program).

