## Discussion

The aim of the study will be to test the effect of APA and/or endometriosis-based education to reduce pain and fatigue and to increase PA in patients with endometriosis. Given the limited effectiveness of current treatment (pharmaceutical treatment and surgery), in order to find a way to help improving the effectiveness of the treatment particularly on QoL, there is a need for assessing the efficacy of non-medical interventions targeting physical and mental health via a relatively low-cost solution: PA. The objective is not to replace current treatment but to include in the treatment protocol non-intervention which could improve QoL. In order to investigate the effectiveness of the intervention, a waitlist control will be recruited and used as the comparator. It was expected that the combined intervention will have more important effect than other interventions and the control group. The separate interventions (i.e., only APA, only endometriosis-based education) are supposed to be equivalent not only for QoL but also for pain and fatigue, but the APA intervention is supposed to increase PA during and after the intervention, regarding the content of the intervention.

If several strengths of this study could be highlighted, some limitations should be also considered. Investigating four arms this study will inform about the effectiveness of the two-intervention components separately and combined. The sample size will be large enough to obtain reliable results. The videoconference modality will ease the recruitment and the adherence for PA sessions. Study about endometriosis and PA are scarce, and this study will help to partly fill this scientific gap.

The use of video of movement and waiting list could result in a Hawthorne effect. However, to control this effect, the same video will be sent to every participant, and the duration of the study should be sufficient to decrease this potential effect. Otherwise, it seems more ethical to propose to participants in the control group to also benefit from a potentially effective treatment. The videoconference modality and online questionnaire induce a selection bias given that only patients with electronic device, numerical literacy, and Internet access will be able to participate. However, if the program is proven to be effective, it could be easily adapted for an on-site intervention.

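### Followed as written, the rule merging arms below 200 participants answers a different question from APA + education versus waitlist, and nothing says that contrast is kept

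*Protocol article*

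**What the plan says.** The Trial design section {8} sets up four arms: "Randomization will be balanced with a 1:1:1:1 ratio". Under the choice of comparators {6b}, "The comparator will be the waitlist control group". The Primary outcome measure section gives the main expectation for QoL: "Greater improvements are expected in the APA + education arm compared to the waitlist control group".

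The section on additional analyses {20b} then gives a conditional rule: "If the sample size of 200 participants cannot be reached, the data from APA and APA + education arms will be gathered together". For the two remaining arms the rule goes on to say that "the same protocol will be planned for control group and education arm". I read this second half as merging the waitlist and education arms with each other. That leaves two groups: APA or APA + education on one side, education or waitlist on the other.

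The Discussion expects the combination to do best and says of the single interventions that they "are supposed to be equivalent not only for QoL but also for pain and fatigue". It names as a strength that four arms will show the components both separately and together. The Background makes the matching criticism of earlier trials, that they could not isolate what each component does.

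**The concern.** After the merge, neither arm of the main comparison exists as a group of its own. The two-group analysis estimates what APA adds, averaged over people with and without education. It does not estimate the effect of the combined programme against waitlist, which is objective I and the primary expectation, and it gives no education effect at all. The article states the rule as something that will happen below 200, and nowhere says that the four-arm comparison is still made.

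The rule appears intended to help a smaller trial by forming larger groups. For QoL, under the protocol's own expectations, it would do the opposite, because half of the merged comparison group receives an intervention that is expected to work.

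**Working it through.** **Inputs from the protocol article.** Allocation is 1:1:1:1 {8}, so there are N/4 per arm and N/2 per merged group. The test is two-sided at 0.05 {20a}. APA and education are supposed equal for QoL (Discussion). The target is 200, with 20% dropout {14}.

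**Assumptions.** The sample size section {14} describes detectable effects only in words, between small and medium, with no number or SD. I set SD = 1 and let the effect of APA + education over waitlist, c, be 0.50, 0.65 or 0.80. The middle value is what 50 per arm detects with 90% power: 0.65/√(2/50) = 3.25, and Φ(3.25 − 1.96) = 0.90.

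**The plan's own figures.** 2 × 7 × 20 = 280, and 280 × 0.8 = 224; both reproduce. For a repeated-measures ANOVA with 4 groups, 5 time points, N = 200 and 90% power (reading the printed β = 0.90 as power), an assumed within-person correlation of 0.3 to 0.7 gives detectable f = 0.18 to 0.23 between groups and 0.08 to 0.12 for group by time. This fits the verbal description, but there is no number to match.

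**Could the rule apply?** The consent section {26a} lists five hospitals, not seven. On five, 2 × 5 × 20 = 200 recruited, and 200 × 0.8 = 160 retained. The rule does not say whether 200 means recruited or retained. I use N = 160 as an illustration, not a forecast: recruitment also runs through media and patient associations {15}.

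**Pooled effect.** Let APA, education and the combination have effects a, e and c over waitlist.

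- Pooled difference = (a + c)/2 − (0 + e)/2.
- With a = e this is c/2, whatever the interaction.

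**Standard errors.**

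- Pairwise: √(2/(N/4)) = √(8/N).
- Pooled: √(2/(N/2)) = √(4/N).
- Ratio of expected z, pooled to pairwise: (1/2) × √2 = 0.71, at every N and every c.

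**Power at N = 160** (SE 0.2236 pairwise, 0.1581 pooled; normal approximation):

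| c (SD) | Pairwise z | Pairwise power | Pooled z | Pooled power |
|---|---|---|---|---|
| 0.50 | 2.24 | 61% | 1.58 | 35% |
| 0.65 | 2.91 | 83% | 2.06 | 54% |
| 0.80 | 3.58 | 95% | 2.53 | 72% |

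At c = 0.65 the pairwise test at N = 100 and the pooled test at N = 200 both have 63% power, so pooling costs as much as halving the sample. Allowing for the extra spread from mixing arms lowers pooled power by a further two points at most in the additive case.

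**Where the direction reverses.** With additive effects, c = a + e and the pooled difference is a. Pooling has the larger z when a√2 > a + e, that is, when e < 0.41a. At N = 160 with c = a = 0.50 and e = 0, pooled power is 89% against 61%.

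**Against adjusted four-arm tests** (N = 160, additive, a = e):

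| c (SD) | Pooled | 3-df omnibus | Bonferroni, 3 tests | Bonferroni, 6 tests |
|---|---|---|---|---|
| 0.40 | 24% | 29% | 27% | 20% |
| 0.50 | 35% | 43% | 44% | 34% |
| 0.65 | 54% | 67% | 70% | 61% |

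**The case against.** The rule sits under additional analyses {20b}, not under the primary and secondary methods {20a}, and it never says that the main comparison is dropped. The four-arm data would still exist, and {20a} refers to a separate statistical analysis plan that is not at hand. This stands as far as it goes: a reader might infer that the protocol abolishes its primary contrast, and the text does not state that. What it does is prescribe a merge and leave the status of the main comparison open.

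The merged comparison is also sound in itself. With equal allocation, education is present on both sides, so it is balanced rather than confounded. The comparison is the APA margin of a 2x2 design. This stands too: the objection is to its use in place of the main contrast, not to its validity.

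Finally, a reader might infer that pooling always has less power than the four-arm analysis. The documents do not support that. Equal component effects are only supposed, and only for QoL, pain and fatigue. For physical activity the Discussion expects the gain to come from APA, and there pooling may well have more power. The comparator used above is a single unadjusted pairwise test. Against an omnibus or Bonferroni-corrected test the gap narrows, and against a six-test correction it disappears at c = 0.50 and slightly reverses at c = 0.40.

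**Conclusion.** The concern holds in a limited form. The protocol prescribes a merge below 200 and does not say that APA + education versus waitlist survives it. If the rule is followed as written, the trial answers a different question and leaves the education and combined-programme effects unestimated, against its stated aims. This part does not depend on any effect size.

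The power loss is conditional. For QoL with equal single-component effects, expected z is 0.71 of that of the unadjusted pairwise contrast, without any assumption on SD or c. The power percentages rest on assumed values of c and on N = 160. The loss reverses under additive effects when education is worth less than about 0.41 of APA.

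**What to change.** Delete the pooling rule as a replacement analysis. State that APA + education versus waitlist on QoL remains the primary contrast whatever N is reached, reported with its confidence interval, at the primary time point that the plan designates. Report the 2x2 margins (APA yes or no, education yes or no, and their interaction) only as a pre-specified secondary analysis. With no analysis depending on the threshold, it no longer matters whether 200 means recruited or retained.

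The cost is a change of wording in the protocol and the analysis plan. The downside is a wider confidence interval for the primary contrast if recruitment falls short.

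### Subgroup analyses triggered by observed baseline differences are the wrong remedy for chance imbalance between arms

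*Protocol article*

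**What the plan says.** Protocol article, Methods for additional analyses {20b}: "If sociodemographic characteristics differ between arms, subgroup analyses will be performed according to the differences found". The next sentence adds: "However, the sample size and the randomization procedure should prevent these issues". The section names no characteristics, gives no criterion for a difference and mentions no interaction test. It also does not say that the subgroup results will be pooled into an adjusted overall estimate.

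Three other sections bear on this:

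- Sequence generation {16a}: "Participants will be randomized to one of the four arms using complete randomization which consist of uniformly distributing them". No blocking or stratification is described. The same section notes that "various methods allows to correct the bias provoked by unbalanced in arms", without naming the methods.
- Sample size {14}: "Two hundred participants will be recruited". Trial design {8} has four arms with equal allocation.
- Statistical methods {20a}: general linear and multilevel models with repeated measures, moderation analyses, and "Two-sided *p* < .05 will be considered statistically significant". It refers to a statistical analysis plan on OSF, which is not at hand.

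**The concern.** The rule responds to one problem with a tool made for another. If a prognostic characteristic is unevenly spread over the arms by chance, the overall difference between arms carries part of that characteristic's effect. Adjusting for the characteristic in the model, or pooling the within-level differences, removes that part. Reporting the levels separately leaves the overall estimate as it was.

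The rule also lets the data choose the subgroups. Which characteristics are examined depends on which happened to differ, so a reader cannot tell how many were eligible. The section on data access {31c} says that the shared participant data will carry no sociodemographic information, so an outside reader could not check what set the rule off.

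At stake are small subgroup results with low power and uncontrolled false-positive risk, offered as the answer to imbalance when they do not correct it.

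**Working it through.** The protocol attaches no figure to this rule, so there is none to reproduce. The checks below use its sample size, number of arms, dropout rate and significance level. Everything else is marked as assumed.

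**1. How often the rule would be triggered by chance.** Assume that a difference means p < .05 and that k independent characteristics are examined. After proper randomisation, P(at least one) = 1 − 0.95^k.

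- k = 3: 14%
- k = 5: 23%
- k = 6: 1 − 0.735 = 26%
- k = 8: 34%
- k = 10: 1 − 0.599 = 40%

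The sample size does not appear in the formula. A larger trial has smaller imbalances, but a significance criterion tightens in step.

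**2. Size of the subgroups.** 200 / 4 = 50 per arm, and an even two-level split (assumed) gives 50 / 2 = 25. After the protocol's 20% dropout, 25 × 0.8 = 20.

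**3. What such a subgroup can detect.** For a pairwise comparison on one post-baseline measure (normal approximation, two-sided 0.05, 90% power), the detectable difference in SD units is (1.960 + 1.282) × √(2/n).

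| n per arm | Detectable difference | Power for 0.5 SD (assumed) |
|---|---|---|
| 50 | 3.242 × 0.200 = 0.65 | 71% |
| 25 | 3.242 × 0.283 = 0.92 | 42% |
| 20 | 3.242 × 0.316 = 1.03 | 35% |

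**4. False positives.** One characteristic with two levels and one contrast gives two tests: 1 − 0.95² = 10%. Two levels and three comparisons with the waitlist group give six tests: 1 − 0.95⁶ = 26%. Independence is assumed. The shared control group makes the second figure approximate.

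**5. Whether separate subgroups repair the overall comparison.** A simulation took two arms of 50, no treatment effect, and a binary characteristic with 50% prevalence worth 0.8 SD (assumed). Of 40,000 trials, 5.8% (about 2,330) had that characteristic imbalanced at p < .05. Among those trials:

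- overall comparison, unadjusted: significant in 10.5%
- overall comparison, adjusted for the characteristic: 5.1%
- at least one of the two separate subgroup tests significant: 8.9%

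Adding the subgroup tests leaves the first figure at 10.5%. Adjustment restores the nominal level.

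**6. The reassurance set against the allocation method.** Section {20b} relies on sample size and the randomisation procedure. Section {16a} chooses a procedure with no balancing mechanism and points to later correction.

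**The case against.** The strongest reply is that this is a minor matter in a section on additional analyses. The main analysis is not replaced, and the protocol defers to a plan on OSF that may name covariates. The trigger rate rests on a test and a number of variables that the protocol does not state. Over all randomisations, the unadjusted comparison keeps its 5% error rate; the 10.5% applies only to trials with a marked imbalance in a strongly prognostic characteristic. A contrast within one level of a characteristic is also free of confounding by it.

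Most of this stands and limits the size of the point. It does not rescue the rule, which is printed as the response to imbalance and promises neither pooling nor adjustment.

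A reader might infer more than the text supports:

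- *The primary estimate will be unadjusted.* Neither {20a} nor {20b} excludes covariates, and a covariate list is commonly left to the analysis plan.
- *The information in baseline quality of life is thrown away.* Baseline is one of the repeated measurements of the primary outcome, so it enters the planned models. How fully it is used depends on the parametrisation.
- *The randomisation is faulty and should be blocked.* Section {16a} gives a reason for complete randomisation, namely unpredictability, which matters in an open-label trial where the principal investigator implements allocation. Unstratified blocks would even out arm counts, not sociodemographic characteristics. Likewise "Randomization will be balanced with a 1:1:1:1 ratio" is compatible with equal-probability allocation, and uneven arm sizes are a different matter from uneven characteristics.
- *The reassurance is false.* It is hedged, it cites sample size as well as the procedure, and it may also refer to the preceding provision on not reaching 200. Chance imbalances do shrink as a trial grows. The wording is optimistic rather than plainly wrong.

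**Conclusion.** The concern holds for the rule itself. Observed baseline differences are a poor trigger for analyses, and separate subgroup results do not correct the overall arm comparison.

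The firm part needs no assumed numbers: the remedy does not address the problem, and the choice of subgroups depends on the data. The subgroup precision (about 0.9 SD detectable at 90% power, against 0.65 SD with all 50 per arm) assumes an even two-level split and a single-measure pairwise comparison; a repeated-measures analysis could do somewhat better. The 26% to 40% trigger rate assumes p < .05 on 6 to 10 independent characteristics.

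The impact is moderate: the change should be made, but the primary analysis is not invalidated. If the OSF plan already fixes covariates and subgroups, what remains is to reconcile the protocol text with it.

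**What to change.** Replace the sentence in {20b} as follows:

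- The primary model adjusts for baseline EHP score, as a covariate or through a common baseline mean in the repeated-measures model, and for a short pre-named list of prognostic covariates (baseline pain is one candidate). It does so whatever imbalance is seen.
- Baseline characteristics are described by arm. Observed differences do not trigger any analysis.
- Subgroup claims are limited to pre-named moderators, tested by arm-by-moderator interaction and labelled exploratory. Moderation analysis is already planned under Objectives {7} and Statistical methods {20a}, so this only requires naming the moderators.

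Soften the following sentence in {20b} to say that randomisation makes systematic differences unlikely, that chance differences can still occur, and that the pre-specified adjustment deals with those in the named covariates. Check the result against the plan on OSF so that both give the same covariates and moderators, and date the change before outcomes are compared by arm.

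The cost is a few lines of wording and one model specification. Allocation, data collection and participants are unaffected.
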